### **3.2. Randomization**

Participants will be allocated into two groups (experimental and control). The allocation sequence will be generated by a website ([www.randomization.com](http://www.randomization.com)). A research assistant not involved in the recruitment will make the randomization and place the sequence in numbered and sealed opaque envelopes. A trained examiner, blinded to the group allocation sequence, will collect pre-intervention measurements. Afterward, a trained research assistant will reveal the contents of these envelopes.

Some actions will be taken in an attempt to blind the volunteers as to the intervention received/group allocation. At baseline, the individual will not be told the difference between interventions. In addition, all devices will be wrapped with an opaque material, so that the respiratory training load is not visualized. Finally, in the evaluation one month after the end of the intervention (week 12) the individuals will be asked if they suspected which group they were allocated to. The same procedure will be performed with the evaluators. The hit rate will be used as an indirect measure of blinding success.

### **3.3. Intervention**

Participants will undergo high-intensity inspiratory and expiratory muscle training (experimental group), or a placebo intervention. Both groups will do the same exercise protocol, the only difference between the two groups will be the presence/absence of the load imposed during training. The Orygen-Dual Valve device will be used, which provides workloads of up to 70 cmH2O, an adequate seal, through a comfortable and flexible mouthpiece.

Individuals will perform a home-based intervention, split into two daily 20-min sessions (morning and afternoon), totaling 40 min per day, seven times a week, during eight weeks. Each daily session will be composed into four blocks of three minutes, with a two-minute rest between blocks.

To monitor adherence to the protocol, individuals will receive a training diary, in which duration and subjective perception of effort will be recorded using the Borg scale, for each intervention day. If necessary, a caregiver will be instructed to assist the individual in completing the diary.

#### **3.3.1. Experimental Group**

The training program will be carried out with the Orygen Dual Valve® (Forumed

S.L., Girona, Spain). Individuals will perform a home-based intervention, split into two daily 20-min sessions (morning and afternoon), totaling 40 min per day, seven times a week, during eight weeks. Each daily session will be composed into four blocks of three minutes, with a two-minute rest between blocks. The initial training load for each participant will be set at 60% of his/her maximal baseline MIP and MEP for both inspiratory and expiratory strength training, respectively. Borg score of dyspnea and effort was also considered for adjusting training intensity, and scores from 4 to 6 were targeted. Once a week, a trained researcher will visit their homes, the MIP and MEP will be measured and the training load will be progressed to ensure that 60% of the new pressure values are maintained.

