### **3.3.2. Control Group**

The control group will also perform the exercises using the Orygen Dual Valve® (Forumed S.L., Girona, Spain) device. A sham intervention will be implemented: the initial resistance of the device will be 0cmH2O, and will be maintained throughout the intervention period - there will be no load progression. All procedures adopted with the experimental group, including the weekly home visit, will also be performed with individuals in the control group. However, there will be no real change in the training load. All devices will be wrapped with an opaque material so that the load or possible respiratory training load is not visualized.

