### **3.4. Outcome measurements**

Outcome measurements will be performed at baseline (week 0), immediately after training (week 8), and one month after training (week 12). In the initial evaluation, clinical and demographic data of all individuals, identification, and characterization of the sample

will be collected.

In all three evaluations, measurements of MIP and MEP, inspiratory muscle endurance, peak cough flow, dyspnea, fatigue, exercise capacity, and quality of life will be performed. An examiner, blinded to the group allocation, will perform all these measurements. All participants will be instructed not to comment on information about the training received.

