### **3.7. Statistical analyzes**

All statistical analyzes will be performed by an independent examiner, blinded to the group allocation. Each participant will be assigned with a unique code. All analyses will be performed using SPSS (SPSS Inc., Chicago, IL, USA). The normality of data distribution will be verified for all continuous numeric variables. Descriptive statistics will be calculated for all outcomes. The effects of the interventions will be analyzed from the collected data using intention-to-treat. Data from the last available evaluation will be used for missed sessions. Two-way ANOVA with repeated measures (2\*3) will be used to evaluate the differences between groups, considering the time factor (considering baseline, post-intervention, and 4-week follow-up), for the variables: inspiratory and expiratory muscle strength, respiratory muscle endurance, peak cough flow, and exercise capacity. The level of significance will be set at 5% and adjusted for multiple comparisons. Data distribution and equality of variance will also be analyzed, to ensure the parametric analysis has been applied correctly. The effect sizes will be calculated to determine the magnitude of the differences between the groups. The differences between the two mean values will be expressed in units of their SD, expressed as Cohen's d, or mean results for the experimental group minus the mean results for the control group, divided by the SD of the control group. Effect sizes between 0.2 and 0.5 will be considered small; between 0.5 and 0.8, medium; and above 0.8, large.

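### Section 3.7 carries the baseline forward for anyone who leaves before week 8, although MIP and MEP are read at weekly home visits in between

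*Protocol*

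**What the plan says.** Section 3.3.1 of the protocol describes the home visits in the experimental arm: "Once a week, a trained researcher will visit their homes, the MIP and MEP will be measured and the training load will be progressed". The only purpose given for these readings is to set the load. Section 3.3.2 says of the controls: "All procedures adopted with the experimental group, including the weekly home visit, will also be performed with individuals in the control group". Weekly MIP and MEP in controls are therefore implied, though not named.

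Section 3.4 places the outcome measurements at weeks 0, 8 and 12 ("In all three evaluations, measurements of MIP and MEP" and the other outcomes) and assigns them to one person: "An examiner, blinded to the group allocation, will perform all these measurements". No blinding, device or manoeuvre protocol is stated for the home readings.

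Section 3.7 fixes a 2 × 3 repeated-measures ANOVA with the time levels "considering baseline, post-intervention, and 4-week follow-up". Its rule for gaps is: "Data from the last available evaluation will be used for missed sessions". Section 3.6 expects 20% dropout and sets 17 participants per group.

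**The concern.** Section 3.7 does not define its term for the value carried forward. Section 3.4 uses the same word for the three formal visits. On that reading a participant who leaves in week 6 enters the analysis at weeks 8 and 12 with the baseline value, that is, with zero change, although about five later readings of each primary outcome exist. The other reading would put a home value, not stated to be blinded, in place of the blinded outcome. Neither is satisfactory.

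The size of the estimated training effect is at stake. A rule that assigns zero change to early leavers dilutes the effect when they are ordinary participants. When they are selected by early response, the error depends on how they were selected. An analysis confined to three visits cannot see that selection, whereas the home readings can show it. There are about 14 completers per arm, so the three or so leavers in each arm matter.

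**Working it through.** **The plan's own figure.** 28 × 1.2 = 33.6, rounded up to 34, or 17 per group, as Section 3.6 states. Dropout of 20% is 0.2 × 17 = 3.4 per arm, leaving 13.6. No effect size or SD is given. A two-sided t test at 5% with 14 per group and power 0.80 implies d of about 1.10.

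**Dropout unrelated to response.** Let p be the fraction leaving before week 8, equal in both arms, and Δ the true week-8 difference in change. With baseline carried forward, leavers contribute zero change, so the expected estimate is (1 − p)Δ.

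- Δ = 10: 0.8 × 10 = 8.0
- Δ = 16: 0.8 × 16 = 12.8 (12.9 in one simulation)

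A simulation with 17 per arm, d = 1.10 in SDs of change, within-person correlation 0.6 or 0.8 and losses spread over weeks 1 to 7 gave 79–80% of the true effect and power of 0.74 to 0.77. The figure of 20% is an upper bound in one respect: a person lost only between weeks 8 and 12 already has a blinded week-8 value.

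**Dropout of poor early responders in the trained arm.** Assumptions, none of them in the protocol:

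- SD 18 cmH2O
- correlations 0.65 (weeks 0–4), 0.60 (weeks 0–8) and 0.85 (weeks 4–8)
- half the effect reached by week 4
- 20% loss per arm, random in controls; in the trained arm logistic in z, the standardised week-4 change, with log-odds slope 0.5 to 4 per SD

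The regression of week-8 change on z has slope 18 × (1 + 0.85 − 0.65 − 0.60) / √(2 × (1 − 0.65)) = 18 × 0.60 / √0.70 = 12.9. With p(z) the chance of leaving, the carry-forward estimate is 0.8Δ + 12.9 × E[(1 − p(z))z].

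| Slope | E[(1 − p)z] | True 10 | True 16 |
|---|---|---|---|
| 0.5 | 0.077 | 9.0 | 13.8 |
| 1 | 0.139 | 9.8 | 14.6 |
| 2 | 0.209 | 10.7 | 15.5 |
| 4 | 0.255 | 11.3 | 16.1 |

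The last row is close to deterministic selection; simulation put its final cell at 16.1 to 16.2. On the same scenarios, within-arm regression imputation from the baseline and the week-4 reading gave estimates within about 0.1 of the truth. This assumes that dropout depends only on what the readings show.

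**Precision.** Variance of the week-8 difference in a likelihood model, with 17 per arm, 3 leavers per arm spread over weeks 1 to 7, and outcome variance set to 1:

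| Correlation | Weeks 0 and 8 only | With weekly readings | Ratio | No dropout | Loss recovered |
|---|---|---|---|---|---|
| 0.6 constant | 0.0914 | 0.0874 | 0.956 | 0.0753 | 25% |
| 0.8 constant | 0.0514 | 0.0485 | 0.943 | 0.0424 | 32% |
| 0.95 per week of lag | 0.0800 | 0.0737 | 0.921 | 0.0659 | 45% |

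The variance is thus about 4–8% lower. As effective numbers per arm, 13.6 / 0.96 = 14.2 and 13.6 / 0.92 = 14.8. Noncentral-t power at d = 1.10 is 0.787 at 13.6, 0.805 at 14.2 and 0.823 at 14.8, a gain of roughly 2 to 4 points.

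**The case against.** The strongest case against is that leaving the home readings out is sound design. The outcome is defined as a blinded measurement. The home readings are taken to set the load, by a visitor who changes it in one arm only, with no stated blinding or measurement protocol. Imputing from them could carry arm-specific error into the primary comparison. Auxiliary variables are also commonly left to a statistical analysis plan, which is not at hand.

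Much of this stands. The home readings should not become outcome data, and leaving out auxiliary predictors contradicts nothing in the protocol. Two things do not stand. First, Section 3.7 itself fixes the three time levels and the fill rule, so this is not a matter the protocol left open. Second, when readings serve only as predictors within arm, a constant shift in one arm is absorbed by that arm's model, and noise lowers their usefulness without entering the outcome.

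A reader might infer that the plan overstates the training effect when poor responders leave. That would be true of a baseline-adjusted completer analysis, which at slopes of 1 to 2 gives about 11.7–12.7 for a true 10 and 17.7–18.6 for a true 16. Section 3.7 does not specify that analysis. Under its carry-forward rule the error is mostly dilution and can go either way.

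A reader might also expect power to rise to 0.836–0.860. That requires every leaver to have readings explaining 50–80% of the week-8 variance and gives the baseline no credit. A week-1 leaver may have no home reading at all.

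**Conclusion.** The point holds as a worthwhile, inexpensive improvement. On the natural reading of Sections 3.4 and 3.7, anyone who leaves before week 8 has the baseline carried forward despite later readings of both primary outcomes. With 20% loss unrelated to response, the week-8 effect is diluted by about a fifth. With response-related loss in the trained arm, the error changes size and sign with a dropout pattern that the planned analysis cannot observe.

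Two parts of the gain should be kept apart. Under random loss, replacing carry-forward is enough to remove the dilution. The home readings add protection when loss follows early response, plus the modest gain in precision.

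The 20% dilution rests on the protocol's dropout rate and on all losses falling before week 8 at equal rates in the arms. The other figures rest on the assumed SD, correlations, course of response and dropout model. It is also an inference that the readings go unused and that controls have them: the fill rule does not expressly exclude home values, and the control readings follow from the general statement in Section 3.3.2.

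**What to change.** In Section 3.7:

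- State that weekly home MIP and MEP are entered in the trial database in both arms, and who takes them.
- For MIP and MEP, replace carry-forward with multiple imputation or a likelihood-based mixed model of the blinded week-0, 8 and 12 values. Use the home readings only as within-arm auxiliary predictors of a missing blinded value.
- Keep the model small, for example the last available home reading alone, given about 14 completers per arm.
- State that a home reading never replaces the blinded evaluation.
- Report a sensitivity analysis without the home readings, since they are not stated to be blinded and may be noisier.

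Section 3.3.2 should name the weekly MIP and MEP readings in controls. The cost is data entry for readings already planned, a slightly larger model and one further analysis; no visit or measurement is added. It should be settled before recruitment, because readings not recorded alike in both arms cannot be recovered later.

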### **3.1. Participants**

A non-probabilistic sample will be recruited from the community through contact with health centers, research groups, and university extension programs. Individuals will be included according to the following criteria: Parkinson's disease diagnosed by a neurologist; ability to walk independently, with or without assistive devices; taking antiparkinsonian medication, and who have been medically stable for at least six months; classified between stages 1-3 of the modified Hoehn & Yahr Scale (SCHENKMAN et al., 2001); maximum inspiratory pressure less or equal to -80 cmH2O or maximum expiratory pressure less or equal to 90 cmH2O. Individuals will be excluded according to the following criteria: possible cognitive impairment as determined by cutoff scores (in points) of the Mini-Mental Status Examination; use of deep brain stimulation (DBS); smokers or who stopped smoking less than six months ago; have been affected by respiratory or cardiac infections in the last month; had any other neurological, musculoskeletal, cardiovascular or respiratory disorders that could affect their ability to perform the tests.

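### No contact after randomisation is set to record adverse events, new illness or the reason for stopping, although training is unsupervised at home and 20% dropout is expected

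*Protocol*

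**What the plan says.** The Protocol gives a stated content to each contact or record after randomisation.

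- **Diary (3.3. Intervention):** "individuals will receive a training diary, in which duration and subjective perception of effort will be recorded using the Borg scale". Its stated purpose is to monitor adherence.
- **Weekly home visit (3.3.1. Experimental Group):** "Once a week, a trained researcher will visit their homes, the MIP and MEP will be measured and the training load will be progressed".
- **The same visit in controls (3.3.2. Control Group):** "All procedures adopted with the experimental group, including the weekly home visit, will also be performed with individuals in the control group", without any real change of load.
- **Weeks 8 and 12 (3.4. Outcome measurements):** "measurements of MIP and MEP, inspiratory muscle endurance, peak cough flow, dyspnea, fatigue, exercise capacity, and quality of life will be performed". The examiner is blinded, and "All participants will be instructed not to comment on information about the training received".
- **Week 12 only (3.2. Randomization):** "the individuals will be asked if they suspected which group they were allocated to".

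Health status is checked at entry. Section 3.1 requires people "taking antiparkinsonian medication, and who have been medically stable for at least six months", and excludes those who "have been affected by respiratory or cardiac infections in the last month". Section 3.6 allows for 20% dropout, and section 3.7 fills missing data from the last available evaluation. The Abstract says that the home training is not directly supervised.

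**The concern.** A respiratory or cardiac infection in the month before entry is important enough to exclude a person. Once training starts, no contact is set to notice one. The weekly visitor goes straight to maximal pressure testing and raises the load, with no specified check on whether the participant has been unwell.

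The same gap covers people who leave. Carrying the last evaluation forward supplies a value for the analysis but no reason for the loss. If more people left the loaded arm than the sham arm, a reader could not tell whether the training, an illness or something unrelated was the cause. Analysts cannot recover information that nobody asked for, so a statistical analysis plan could not repair this. Section 1.3 found no study of combined inspiratory and expiratory training in Parkinson's disease, so the document offers no harms record for this combination to lean on.

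**Working it through.** **Step 1. Set the contacts side by side.**

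| Contact or record | Stated content | Events, illness or reason for stopping? |
|---|---|---|
| Diary (3.3) | Duration, Borg effort | No |
| Weekly visit, trained arm (3.3.1) | MIP, MEP, load reset to 60% | No |
| Weekly visit, sham arm (3.3.2) | Same procedures, load unchanged | No |
| Weeks 8 and 12 (3.4) | MIP, MEP, endurance, cough flow, dyspnea, fatigue, walk test, quality of life | No |
| Week 12 extra (3.2) | Guess of allocation | No |

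**Step 2. Look for the nearest substitutes.**
- Borg dyspnea and effort, with a target of 4 to 6, are used to adjust intensity (3.3.1). This is a tolerance signal for setting the load.
- The MRC scale (3.5.2.3) and the Fatigue Severity Scale (3.5.2.4) give dyspnea and fatigue by arm at weeks 8 and 12. Two plausible unwanted effects of loaded breathing are therefore measured.
- Diary duration can show that training lapsed.

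None of these records an event, its date, its seriousness or a reason for stopping.

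**Step 3. Size of the expected loss.** Inputs from section 3.6: 28 evaluable, 20% dropout, 34 enrolled.
- The plan's own figure: 28 × 1.20 = 33.6, rounded up to 34, or 17 per arm. It reproduces. (Dividing instead, 28 / 0.80 = 35.)
- Losses allowed for: 34 − 28 = 6, or 0.20 × 34 = 6.8. That is 6 to 7 people, with no procedure specified to record why they left.

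**Step 4. What recording could show.** With 17 trained participants and no events seen, the one-sided 95% upper limit on the risk is 1 − 0.05^(1/17) = 0.162, or 16.2%. Recording at this size can describe harms; it cannot establish safety.

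**The case against.** The strongest reply is that the protocol is silent rather than wrong. Nothing in it says that events will go unrecorded. Home visitors may note them informally, section 3.0 commits the trial to ethics review and to CONSORT, and the consent pages, which might hold contact or stopping instructions, are not available. Safety is not an objective. Entry is limited to medically stable people at Hoehn & Yahr stages 1-3, the load follows re-measured pressures and Borg scores, and the device stops at 70 cmH2O.

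Most of this stands and limits the point. It does not remove it: what is asked at a home visit is a protocol matter, this protocol lists what is done there, and informal notes need not be comparable between arms. A commitment to a reporting guideline sets no collection step.

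A reader might also infer four stronger things that the document does not support.
- *That harms and reasons will certainly go unrecorded.* The text shows only that no procedure is specified.
- *That the efficacy result is biased.* Recording a reason would not change the planned comparison of muscle strength.
- *That this regimen is more hazardous than earlier ones.* It has 7 × 8 = 56 training days, against 12 × 5 = 60 to 12 × 6 = 72 in the 12-week inspiratory trial. Its 60% load lies within the ranges quoted in section 1.3 (15% to 60% of MIP, 50% to 75% of MEP). Higher exposure is not shown.
- *That participants are told not to report problems.* The instruction in section 3.4 protects assessor blinding and does not bar telling the home visitor about an illness. At most it may discourage volunteering a training-related problem to the examiner.

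**Conclusion.** The point holds as an omission in the content of the contacts. Followed as written, the trial would have dyspnea, fatigue and Borg data, but no systematic record by arm of adverse events, new illness or reasons for withdrawal. About 6 to 7 of 34 participants are allowed for as losses; that is a sample-size allowance and not a forecast. The primary and secondary efficacy results are untouched. What is lost is the ability to interpret withdrawals and to say anything orderly about harm, plus a simple safety check before testing and load progression. The conclusion rests on the visible methods text and makes no claim about the consent pages. It should be corrected because the remedy is small and the missing information cannot be rebuilt afterwards.

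**What to change.** Add the following to the protocol, identically in both arms.

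1. **Weekly visit:** before MIP/MEP testing or any load change, ask one fixed question on new illness, adverse events and hospital contact. Note the onset date and seriousness. If the participant is unwell, hold load progression.
2. **Weeks 8 and 12:** use a self-completed form with the same question, which the blinded examiner does not see.
3. **Anyone who stops or misses a contact:** record the date and reason by a brief phone call or exit form. Waiting for the next visit would miss those who leave the study altogether.
4. **Reporting:** give events and withdrawal reasons by arm, descriptively, through week 12.

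**Cost.** No new visits are needed. With eight weekly visits and full attendance there are at most 34 × 8 = 272 questions. At an assumed 2 to 5 minutes each, that is 272 × 2 / 60 = 9.1 to 272 × 5 / 60 = 22.7 hours over the whole trial. To this add up to 34 × 2 = 68 short forms and a call or exit form for each person who stops or misses a contact. Whoever sets the load in effect knows the allocation, so the weekly reports will carry some bias. Fixed wording in both arms reduces this but does not remove it.
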